### Bipolar Group Support treatment arm

The purpose of the Bipolar Group Support intervention is to provide an active control for the bipolar psychoeducation group, which reflects the practice of expert patient and some types of support groups for bipolar disorder in England. The support groups aim to enable the group participants to devise ways of remaining well, through discussion of collective experience, mutual information sharing and support. Although the groups are unstructured, they are peer led and collectively decide upon an agenda for discussion. Thus these groups do not merely provide a meeting place where people with bipolar disorder can meet other people with bipolar disorder but also have a shared sense of purpose to actively seek ways of learning from the group, to remain well in the future. Therefore the Bipolar Group Support not only provides a control for the processes of delivering a group intervention but also in the overall aim of the intervention for each participant, namely to stay well over time. As a result the groups only differ in terms of the content and style of delivery. The two health professionals and one expert patient meet with the groups of up to 18 participants but are there to facilitate discussion, encourage participation, prevent unhelpful group behaviour such as bullying or scapegoating, to prevent factual misinformation, and if directly asked to clear up factual uncertainty. A manual on the conduct of the bipolar support group is produced for the therapists and given as a handout in the first session. The supervision arrangements and recording of the conduct and content of the sessions are the same as for the group psychoeducation sessions.

Both groups of patients will receive the trial group therapies in addition to their usual treatment. The latter is unconstrained and recorded from case notes and at the economic interview.

### Randomisation and treatment allocation

Randomisation is conducted by a clinical trials unit at the University of Nottingham, who will be given the participant information by the programme manager or programme administrator. Randomisation is only undertaken once a group of 20 participants in a wave (figure 1) have been identified, since this is the minimum number that would constitute a viable group size. Maximum group allocation is 36. Allocation of participants to treatment is based on stochastic minimisation using number of previous episodes banded as (<7, 8-19, 20+) and clinical site. The clinical trials unit conveys the allocation to the trial manager who contacts the participants themselves and the therapists conducting the group. The research assistants are blind to group allocation. All information regarding group treatment and cohesion is collected by the therapists so that RAs remain blind. Any subsequent unblindings are recorded by the trial office. Where possible once an RA has been unblinded an alternative RA at that site collects the remainder of that participants follow-up data.

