• The Hypomania Interpretations Questionnaire [38], a 10-item self-report questionnaire to explore if either group changed positive self-dispositional appraisals for hypomania-related experiences.

• The Social Rhythm Metric [39,40] trait and diary forms are completed over one week. The habitual timing of 17 daily behaviours is assessed.providing information on the number, timing and frequency of occurrence of regular activities.

• The Short-Form 12 (SF-12) [41], a 12-item self-completed questionnaire evaluating eight domains of overall health (general health, role physical, physical function, bodily pain, vitality, social functioning, role emotional, and mental health) in the preceding four weeks summarised as physical component scores and mental component scores.

• The Early Warning Signs checklist [42], a 32-item and 31-item checklist of common early warning signs of depression and mania, and the timing of these signs in relation to the onset of a depressive or mania episode respectively.

• The Coping Strategies Checklist [20], a list of adaptive and maladaptive coping strategies employed with the onset of manic symptoms (40 items) [43] and depression (40 items) symptoms. The coping with depression checklist was derived from items from the Response Style Questionnaire [44], the Depression Coping Checklist [45], items from the coping with mania questionnaire [43] that were also relevant to depression according to a panel of service users from a UK service user organisation (the Bipolar Organisation: the Manic Depression Fellowship) plus four additional items suggested by these service users.

• The Brief Illness Perception Questionnaire [20,46], a 11-item self-report measure of beliefs about mood swings in bipolar disorder, each measure on a five point scale of strength of conviction.

In addition, weekly ratings of treatment fidelity for each treatment session during the 21 session treatment are taken using a short checklist designed specifically for this study. Participants are asked to provide feedback specifically on group cohesion [47] and group working alliance (WAI-S) [48] which are administered at weeks 3, 10 and 21 of follow-up.

Follow-up of each patient is for 96 weeks from randomisation. Patients who had not relapsed at 96 weeks are censored on the time to next bipolar episode outcome. SCID-LIFE interviews to collect time to next relapse are collected every 16 weeks alternating between telephone and face to face interview up to 96 weeks.

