An aim of the bipolar group psychoeducation arm is for each participant to develop their own individualised relapse prevention programme (a "stay well plan"). This includes a list of people that it might be shared with including family members and clinicians, but the final decision on whether to share the care plan rests with the participant. The expert patient and health professionals taking the group are supervised by RM in the East Midlands and FL & SJ in the North West. In addition, the expert patients taking part in the groups can take part in a peer run supervisory group in the North West run by DM. The content and conduct of each session are recorded on written forms firstly by the therapists and then also by the participants (with the therapists not present) using the treatment fidelity checklist. The group sessions have not been audiotaped because if one or more participants did not agree then a session could not be taped.

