The main strengths of the RCT are the size of the sample and its multi-site design allowing consistency of intervention effects and their generalisability to be explored. Unlike a psychological treatment study compared against treatment as usual or a briefer intervention, it may be possible to achieve independent and blinded rating of outcome because both interventions are similar in form and duration but differing in content. Outcomes are assessed using well-validated measures that we have applied successfully before in a series of RCTs on psychological interventions in bipolar disorder. Furthermore although the trial has a clear theoretical aim, it is carried out using methods that are relatively close to usual clinical practice settings, again allowing the results to be readily generalisable to routine clinical practice. The combination of qualitative and quantitative data collection around mechanisms of action, the nature of the intervention and its effects, and barriers to its delivery allows sufficient detail both to replicate these complex interventions and optimise their delivery for both further research and clinical practice [62].

The main weakness of the current RCT is the lack of a treatment as usual group. Whilst the trial will report on the relative clinical and cost effectiveness of the two interventions it cannot definitively show that either is more clinical or cost effective than treatment as usual. The process measures will be able to track whether key processes are changing in the groups, particularly in the group psychoeducation intervention. Thus, in both groups there should be evidence of group cohesion if these interventions are likely to be effective but in addition the specific content of the group psychoeducation intervention should show improvements in knowledge about bipolar disorder, early warning signs and adaptive strategies, and regularity of social rhythm coping. If such changes are not happening over time in the participants who have adhered to the group psychoeducation, then it is less likely that group psychoeducation had been effective in this RCT. While group psychoeducation has demonstrated improvements in medication adherence [63], previous psychological treatment studies performed by our group [21,51] have not demonstrated such benefits because of ceiling effects with high levels of medication adherence in both intervention and treatment as usual groups.

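### Therapists collect participants' ratings of their own groups with no stated safeguard, and keeping the research assistants blind does not require it

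*Protocol article*

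**What the plan says.** The Protocol article deals with these ratings in four places.

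- **Baseline and Outcome Measures** says who gives the ratings: "Participants are asked to provide feedback specifically on group cohesion [47] and group working alliance (WAI-S) [48". There are three rating occasions, in weeks 3, 10 and 21. The section does not say who hands out or receives the forms, and neither scale appears in Table 1.
- **Randomisation and treatment allocation** gives the collection rule: "All information regarding group treatment and cohesion is collected by the therapists so that RAs remain blind". Just before this it states the aim that the rule serves: "The research assistants are blind to group allocation". The same paragraph has the clinical trials unit pass allocations to the trial manager, who then contacts participants and therapists.
- **Group Psychoeducation** describes another form that participants fill in about the sessions. Therapists record each session first, "then also by the participants (with the therapists not present) using the treatment fidelity checklist". **Bipolar Group Support treatment arm** extends this to the other arm: "recording of the conduct and content of the sessions are the same as for the group psychoeducation sessions".
- **Discussion** says how cohesion will be read: "in both groups there should be evidence of group cohesion if these interventions are likely to be effective".

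**The concern.** Cohesion is a participant's judgement of the group, and working alliance is a judgement of how the group works together with those who lead it. If the leaders gather those judgements, participants may answer more kindly than they otherwise would. The article gives no step that guards against this for the two scales, although it has one for the fidelity checklist.

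The stake is the process evidence. The Discussion names the missing treatment-as-usual arm as the main weakness and then turns to the process measures for some reassurance. Cohesion in both arms is one of the conditions it sets. If that condition looked met only because of how the forms were gathered, the reassurance would be worth less than it seems.

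**Working it through.** No figure in the plan needs reproducing and no test or sample-size formula is involved. The check sets the passages side by side.

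**1. Does the rule cover both scales?** Cohesion is named in the rule. WAI-S is not; it comes in only if information on group treatment is read to include a group alliance scale given during treatment. That is the natural reading, but it is an inference.

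**2. Does assessor blinding require the rule?** Blinding requires that the forms do not pass through the research assistants. It does not require that they pass through the therapists. The trial manager already receives the allocations, so forms returned there reveal nothing new to that person and nothing to the research assistants. The trial also already uses e-mail and reply-paid post for self-rated questionnaires at 16, 48 and 80 weeks, so a route that avoids the therapists is familiar, although the article does not say who opens that post.

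**3. Does the protocol already have the safeguard?** In part. Participants complete the fidelity checklist with therapists absent, in both arms. That concerns who is in the room, not who receives the form. Read literally, the collection rule would cover the fidelity forms too. The checklist step is therefore a useful model for completion but does not settle the return route.

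**4. Would a shift common to both arms matter?** Let the true mean cohesion be A in one arm and B in the other, and let the collection method add a to the first and b to the second.

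- Observed difference = (A − B) + (a − b). If a = b, the shift cancels.
- Observed level in each arm = A + a and B + b. The shift stays even if a = b.

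The Discussion asks whether cohesion is present in each arm, which is the second kind of reading. The documents give no value for a or b.

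**5. How many ratings are exposed?**

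- Upper bound: the planned 358 participants (179 per arm) × 3 occasions = 1,074 ratings per scale.
- More realistic: the Group Psychoeducation section expects that 25% may not attend, leaving 12 to 14 per group. Sample size gives 10 groups per arm, so 20 in all. 20 × 12 = 240 and 20 × 14 = 280 participants. Over three occasions that is 720 to 840 ratings per scale. This assumes that the support groups shrink to the same size.

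**The case against.** The best defence is that the article says only who collects the information. It does not say that therapists are present when the forms are filled in, that they read the answers, or that the envelopes are open. The fidelity checklist shows that, in this trial, a form can fall under therapist collection and still be completed in their absence. Who seals and carries a form is also the sort of detail that a journal article leaves to the full protocol.

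Much of this stands. It rules out several stronger conclusions that a reader might infer:

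- *That the ratings are biased upward.* This is a plausible risk. Nothing in the article shows its presence, size or direction.
- *That scores reach a ceiling and the difference between arms is compressed.* This needs data that the article does not contain. The method is the same in both arms, so any shift could be similar in each.
- *That the therapists themselves are what is rated.* Cohesion concerns the group, and the alliance measure is described as a group one.
- *That the trial's answer on content versus group process rests on these scores.* That answer comes from the randomised comparison on time to next episode. The Discussion also draws on knowledge, early warning signs, coping and social rhythm, and participants' experience is studied separately by interview.

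The defence does not remove the point that remains. The collection rule is not an omitted detail: the article states it, with a reason, and that reason does not call for it.

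**Conclusion.** The point holds as a minor, easily repaired weakness in a process measure. Therapists collect participants' cohesion ratings, and by a reasonable reading their WAI-S ratings, with no stated safeguard and for a reason that another route would serve equally well. The consequence is a risk of inflated scores where the Discussion reads cohesion in absolute terms. Its size cannot be calculated.

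The primary outcome comes from SCID-LIFE interviews by research assistants intended to be blind, so neither it nor the randomised comparison based on it is affected.

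This rests on two assumptions: that the rule includes WAI-S, and that no sealed or therapist-absent procedure for these scales stands in the full protocol, which is not shown.

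**What to change.** Amend the rule under Randomisation and treatment allocation so that:

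1. participants complete the cohesion and WAI-S forms with the therapists out of the room, as for the fidelity checklist;
2. participants seal the forms, which are returned to the trial manager, not to the therapists or the research assistants;
3. participants are told beforehand that therapists will not see individual answers.

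If this is already the practice, one clarifying sentence is enough.

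The cost is envelopes and a line in the procedures, with no added visits, staff or participants. There is one small drawback. The Results section says that the trial is already recruiting, so groups assessed before and after the change may not be strictly comparable on these scales. Record which waves used which procedure and flag them when cohesion is summarised.

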### Qualitative studies

Barriers (attitudinal, experiential and practical) to the effectiveness of group psychoeducation are assessed using audiotaped and transcribed semi-structured qualitative interviews with maximum variance samples of group leaders (health professionals and expert patients) and patients. The transcripts are thematically analysed with reference to a multidisciplinary group. The main focus of the qualitative work relates to the: 1) feasibility of delivering group psychoeducation for relapse prevention in bipolar disorder; 2) key differences in the experience and future relapse prevention care planning of participants in the bipolar group psychoeducation and bipolar group support treatment arms; 3) issues arising from involving expert patients as co-therapists with health professionals (health professionals and expert patients are keeping reflective diaries of their experiences of running the groups); and 4) application of their "stay well plans" after the groups have finished, including their acceptance and help with delivery by health professionals.

### Analysis

Intention to treat using Kaplan-Meier recurrence-free curves with significance tests will be based on the Cox proportional hazards regression model. The level of dependence or heterogeneity among patterns of recurrence

within the same team was estimated by the intracluster correlation coefficient (ICC) using estimate of frailty from the shared frailty model [60]. Trial centre, and number of previous episodes of bipolar disorder, will be included as covariates. Analysis of quantitative secondary outcome measures will use linear mixed models including baseline covariates and random effects for therapy group [52]. The treatment effect may differ according to illness duration/number of episodes with a lesser treatment effect in patients with longer illness duration/more episodes based on findings of the MRC CBT trial [21]. This will be tested in a secondary analysis by adding a severity-treatment interaction into the above models.

The economic analysis will be adjusted for baseline covariates shown to be important predictors of future costs and outcomes (e.g. costs and service use prior to entry, health status and utility, clinical severity and duration of illness, socio-economic status). Bootstrap simulations will be used to estimate cost effectiveness acceptability, net benefit statistics and the likelihood that group psycho-education is cost effective compared to group support. Probabilistic simulation models will be used to explore the generalisability of the results to the UK.

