**Methods/design:**

Single blind two centre cluster randomised controlled trial of 21 sessions group psychoeducation versus 21 sessions group peer support in adults with bipolar 1 or 2 disorder, not in current episode but relapsed in the previous two years. Individual randomisation is to either group at each site. The groups are carefully matched for the number and type of therapists, length and frequency of the interventions and overall aim of the groups but differ in content and style of delivery. The primary outcome is time to next bipolar episode with measures of the therapeutic process, barriers and drivers to the effective delivery of the interventions and economic analysis. Follow up is for 96 weeks after randomisation.

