### Sample size

When patients receive treatment in groups, interactions between patients may lead to correlation of outcomes of patients in the same group [52] sometimes referred to as cluster. As with cluster randomised trials, sample size calculation needs to consider the possibility of intra-cluster correlation [53]. As there are no previous trials of group interventions for bipolar disorder that have considered clustering, we considered empirical evidence regarding the magnitude of clustering from cluster randomised trials. A previous trial [54] found a negligible clustering effect (0.0001) but this was from a small sample, and so would be imprecisely estimated. We have therefore assumed a small but not zero clustering effect equal to 0.05. Based on the outcomes from the two previous Barcelona protocol psychoeducation randomised controlled trials [7,8] a differential treatment effect of 0.22 was used (60% recurrence in the control group, 38% in the psychoeducation group). Power for 80% probability of detecting a difference at 0.05 level, 2-tailed testing requires 82 patients per arm. Assuming a mean group size of 18 and an intra-cluster correlation coefficient of 0.05, a design effect of 1.85 gives a sample size of 152 in each arm. We have assumed 15% loss to follow up [54] giving a total sample size of 179 per arm (358 in total). This is achieved by running 10 groups of 18 subjects in each arm (10 in the North West and 10 in the East Midlands) over 3 years. Initially 17-18 patents are recruited per group but with attrition there will be 13-14 patients per group, the ideal size for group psychoeducation based on 10 years experience [55].

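### The primary Cox analysis names the wrong clustering unit (team, not therapy group) and does not put the frailty term into the test of treatment

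*Protocol article*

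**What the plan says.** The Sample size section of the Protocol article takes the therapy group as the cluster. It argues that "interactions between patients may lead to correlation of outcomes of patients in the same group" and sets the size of that correlation: "We have therefore assumed a small but not zero clustering effect equal to 0.05". With 18 patients per group it multiplies the sample size by 1.85 and plans 10 groups per arm.

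The Analysis section, on the primary outcome (time to next bipolar episode), says that "significance tests will be based on the Cox proportional hazards regression model". It then says that the dependence among patterns of recurrence "within the same team was estimated by the intracluster correlation coefficient (ICC) using estimate of frailty from the shared frailty model". The covariates named are trial centre and number of previous episodes.

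The next sentence of that section gives the quantitative secondary outcomes linear mixed models with a random effect at therapy-group level.

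Patients are individually randomised, with stratification by clinical site (Design section). *Team* is not defined as a unit of the trial. Outside the Analysis section the word refers to community mental health teams, in the Setting section and the Discussion, or to the research team.

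**The concern.** The same document uses the therapy group as the cluster when it sizes the trial and when it models the secondary outcomes, but names a different unit for the primary outcome. It mentions the frailty model as the means of estimating an ICC, and does not say that the frailty term is in the model that tests treatment.

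Therapy groups are nested within arm, so variation between groups adds directly to the variance of the treatment comparison. A Cox test with no group term leaves that variation out of its standard error. A frailty on a clinical team or site does not help. Allocation is individual within site, so such a unit would hold patients of both arms, and its frailty does not absorb differences between the two therapy groups run there.

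At stake are the primary p-value and confidence interval. There is also room, once the data are in, to choose between an adjusted and an unadjusted primary result.

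**Working it through.** **Inputs** (Protocol article, Sample size section): two-sided alpha 0.05 and 80% power ("Power for 80% probability of detecting a difference at 0.05 level, 2-tailed testing requires 82 patients per arm"); recurrence "60% recurrence in the control group, 38% in the psychoeducation group"; ICC 0.05; 18 per group; 15% loss to follow-up; 13 to 14 per group after attrition; 10 groups per arm.

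**Step 1: the plan's own figures.**
- The usual two-proportion formula for 60% against 38% gives 80 per arm. The stated 82 is within two patients.
- Design effect: 1 + (18 − 1) × 0.05 = 1.85.
- 82 × 1.85 = 151.7, so 152 per arm.
- 152 / 0.85 = 178.8, so 179 per arm.

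The chain reproduces, and its cluster is the therapy group.

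**Step 2: a test that ignores the group.** If the true variance is D times the variance assumed, with D = 1 + (m − 1) × ICC, the real two-sided type I error is 2 × (1 − Φ(1.96 / √D)).

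| Analysed per group, m | D at ICC 0.05 | Type I error at ICC 0.05 | Type I error at ICC 0.01 |
|---|---|---|---|
| 13 | 1.60 | 12.1% | 6.4% |
| 14 | 1.65 | 12.7% | 6.5% |
| 15.3 (18 less 15%) | 1.715 | 13.5% | 6.7% |
| 18 | 1.85 | 15.0% | 7.0% |

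At the ICC of 0.0001 that the Sample size section quotes from an earlier trial, the result is 5.0%.

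**Step 3: check by simulation.** The set-up had ten pairs of groups, one group per arm at each site. A log-normal frailty was set to give an ICC of 0.05 for recurrence by the end of follow-up. Overall recurrence was 49% or 60%, m was 14, 15 or 18, and there were 3,000 runs per setting. The test was the log-rank test, which is the score test of a Cox model with treatment alone. A version stratified by site stands in for adjustment on a unit that holds both arms.

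| Where the clustering lies | Unadjusted test | Stratified by site |
|---|---|---|
| All specific to the therapy group | 12.4% to 16.7% | 13.5% to 17.6% |
| Half shared by both arms of a site | 7.5% to 10.1% | 8.6% to 11.1% |
| All shared by both arms of a site | 3.8% to 4.9% | 4.5% to 5.7% |

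With 3,000 runs, the standard error of a rate near 14% is √(0.14 × 0.86 / 3000) = 0.6 percentage points, so small differences between settings should not be read into. The first row agrees with Step 2. It also shows that adjusting on a unit that contains both arms does not protect the test.

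**The case against.** The strongest reply is that the shared frailty model may be meant as the primary model. The section moves from Cox regression to shared frailty and then to covariates, and later adds an interaction to the models described before it. A shared frailty model is normally a proportional hazards model with a random effect for cluster, so estimating the frailty means fitting that model. *Team* may be a slip: the sentence is in the past tense within a plan otherwise written in the future tense, which suggests carried-over wording, and the unit is correct elsewhere. This largely stands. A reader might infer that the primary p-value will run at 12% to 15%. The document does not support that; it supports only that this would follow if the text were applied literally.

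Second, 0.05 is a cautious choice informed by cluster randomised trials, whose ICCs can include variation between sites. Here both arms run at each site, so that part largely cancels. This stands too, and is why a range is given. Against it, 0.05 within the group is the value the plan chose and sized the trial for.

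Third, the top of the range needs all 18 per group to be analysed. That is fair. But 13 to 14 is the number expected in the group after attrition, while the analysis is by intention to treat and seeks recurrences from case notes and key workers for those who leave direct follow-up. A figure between the ends of the range is plausible.

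Two further inferences are tempting. The article says "Bootstrap simulations will be used to estimate cost effectiveness acceptability, net benefit statistics" with no mention of groups, and a reader might conclude that the economic analysis ignores clustering. An article commonly leaves the resampling scheme to the full plan, and nothing stated there is wrong. The abstract also says "Single blind two centre cluster randomised controlled trial", but its next sentence states individual randomisation and the Design section confirms it. That is a labelling matter and does not alter the primary test.

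**Conclusion.** The point holds as a fault in what the Analysis section states. It names the wrong clustering unit for the primary outcome and does not place the frailty term in the test of treatment.

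The consequence is conditional. Without a therapy-group term, or with frailty on a unit that holds both arms, the two-sided type I error is about 12% (13 per group) to 15% (18 per group). This assumes that all of the ICC of 0.05 is specific to the therapy group. If half of the clustering is shared by both arms of a site, the figure is about 8% to 10%; at an ICC of 0.01 it is about 6% to 7%. If the frailty is indexed by therapy group and used for the test, the error is close to the nominal 5%.

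The document does not settle which of these applies. Because this is the primary test, it should be settled in the text before analysis.

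**What to change.** In the Analysis section, replace *team* with *therapy group*. State that the primary treatment effect, with its confidence interval and p-value, comes from a Cox model with shared frailty (or group-robust variance) indexed by therapy group, with centre and number of previous episodes as covariates. Put the sentence in the future tense. The handling of the small number of groups (20) can be left to the analysis plan.

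The cost is a few words and little programming. The standard error grows by √1.60 = 1.26 at 13 per group and √1.85 = 1.36 at 18 per group if the ICC is 0.05. The sample size already pays for this through the design effect of 1.85, so no more patients are needed on this account.

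### The Analysis section does not state that the primary Cox test accounts for clustering by therapy group, and it places the frailty on an undefined "team"

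*Protocol article*

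**What the plan says.** All references are to the protocol article.

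- **Analysis, primary outcome.** The "significance tests will be based on the Cox proportional hazards regression model". The next sentence says that dependence or heterogeneity in recurrence "within the same team was estimated by the intracluster correlation coefficient (ICC) using estimate of frailty from the shared frailty model". Trial centre and number of previous episodes are then listed as covariates. Therapy group is not mentioned for this outcome.
- **Analysis, quantitative secondary outcomes.** These use "linear mixed models including baseline covariates and random effects for therapy group".
- **Sample size.** Clustering is attributed to patients being treated together in a group, and the size is inflated for it: "Assuming a mean group size of 18 and an intra-cluster correlation coefficient of 0.05, a design effect of 1.85 gives a sample size of 152" per arm. The plan is for 10 groups per arm.
- **Design; Randomisation and treatment allocation.** Patients are individually randomised, with allocation balanced by clinical site and number of previous episodes.
- **Abstract, Methods/design.** The trial is called a "Single blind two centre cluster randomised controlled trial", although the following sentence describes individual randomisation.

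**The concern.** Patients are randomised one by one and then treated in about 20 closed therapy groups, each belonging to a single arm. Variation between therapy groups therefore adds directly to the error of the arm comparison, which is why the Sample size section applies a design effect. The primary analysis has to carry the same source of variation, or its p-value and interval understate the uncertainty.

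As written, the Analysis section leaves two things open for the primary outcome. It does not say that the frailty term is in the model that gives the treatment test. It also names "team", a word the article never defines as a therapy group. In clinical contexts elsewhere (Setting, Discussion) it means a community mental health team or a crisis and home treatment team.

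Time to next manic-type episode and time to next depressive episode share the gap, because the therapy-group random effect is promised only for quantitative secondary outcomes. At stake are the type I error and the interval coverage of the trial's main result.

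**Working it through.** **1. Reproduce the plan's sample size.** Inputs from the Sample size section: "60% recurrence in the control group, 38% in the psychoeducation group", two-sided 0.05, 80% power, group size 18, ICC 0.05, 15% loss.

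- Two proportions, pooled variance, mean proportion 0.49: n = [1.96·√(2·0.49·0.51) + 0.842·√(0.60·0.40 + 0.38·0.62)]² / 0.22² = 80 per arm. The plan states 82, a difference of 2 patients.
- Design effect: 1 + (18 − 1)·0.05 = 1.85, as stated.
- 82 × 1.85 = 151.7, so 152. Then 152 / 0.85 = 178.8, so 179 per arm and 358 in total, as stated.

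The sizing is sound and does allow for therapy-group clustering.

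**2. Compare the clustering unit across the article.**

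| Place | Unit |
|---|---|
| Sample size | therapy group |
| Quantitative secondary outcomes | therapy group |
| Primary outcome | "team", in a sentence about estimating an ICC |

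**3. Size of a test that omits therapy group.** If the variance is understated by the design effect DE = 1 + (m − 1)·ICC, the true two-sided error of a nominal 5% test is 2·[1 − Φ(1.96/√DE)]. The correct interval is √DE times as wide as the one reported. The value m = 15.2 is 152/10, the group size analysed after 15% loss. The values 13 and 14 are the group sizes after attrition given in the Sample size section.

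| m | ICC | DE | True alpha | Width factor √DE |
|---|---|---|---|---|
| 18 | 0.05 | 1.85 | 0.150 | 1.36 |
| 15.2 | 0.05 | 1.71 | 0.134 | 1.31 |
| 14 | 0.05 | 1.65 | 0.127 | 1.28 |
| 13 | 0.05 | 1.60 | 0.121 | 1.26 |
| 18 | 0.10 | 2.70 | 0.233 | 1.64 |
| 18 | 0.02 | 1.34 | 0.090 | 1.16 |
| 18 | 0.01 | 1.17 | 0.070 | 1.08 |
| 18 | 0.0001 | 1.002 | 0.050 | 1.00 |

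ICC 0.05 is the protocol's assumption and 0.0001 is the estimate it cites from an earlier trial. The values 0.01, 0.02 and 0.10 are assumed here to show the range. At m = 18 and ICC 0.05 a nominal 95% interval covers about 85%, and its width is 1/1.36 = 0.735 of what it should be, so it is about 26% too narrow.

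**4. Check by simulation on survival times.** Under the null, with 10 groups per arm, gamma frailty, a binary ICC of about 0.052 and 6,000 runs, a log-rank test that ignores groups rejects in 16.6% of runs at 18 per group and 14.0% at 15.

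**5. What a frailty on a unit that crosses the arms would do.** Allocation is individual and balanced by site, so a community team or site contains patients from both arms. A random effect on such a unit takes out variation shared by both arms. It cannot take out variation between therapy groups, each of which lies within one arm. A second null simulation (20 groups of 15, lognormal frailty giving a binary ICC of 0.05, 4,000 runs) shows this: 13.1% rejection ignoring clustering, 12.3% when stratified by teams that cross the arms, and 4.3% for a test at therapy-group level.

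**The case against.** The strongest reply is that the text can be read as correct. A shared frailty model is ordinarily a Cox model with a random cluster effect, and the covariate sentence follows it directly, so a single model may be meant to give the test, the ICC and the covariate adjustment. The Sample size section says the therapy group is what is sometimes called a cluster, and the Analysis section speaks of an intracluster coefficient, so "team" may be loose wording for therapy group. The analysis plan, which is not shown, may settle both points.

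That reading is possible, and it rules out some stronger inferences:

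- **That the primary test is an unadjusted Cox model with clustering kept out of the p-value.** The article does not say this. It only fails to say that clustering is in.
- **That "team" must mean community mental health team.** The word is also used for crisis teams and for the research team, so its meaning here is undefined.
- **That the sentence was carried over from a trial that randomised teams.** The past tense and the abstract's label might suggest it, but nothing in the article can confirm it.
- **That the error rate is 13 to 15% as a matter of fact.** This needs therapy group to be absent from the test and an ICC near 0.05. At the cited 0.0001 there is no inflation, although the protocol itself sets that estimate aside as imprecise.

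The reply does not remove the point. The charitable reading needs both "team" to mean therapy group and the frailty model to be the one that gives the primary test, and the article states neither. This is a wrong or undefined unit written down for the primary outcome, next to the right unit for the secondary outcomes. It is more than detail left to an analysis plan.

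**Conclusion.** The concern holds in a limited form. The Analysis section does not state that the primary Cox test accounts for therapy-group clustering, and its stated frailty unit differs from the one the trial was sized for.

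The consequence is conditional. If therapy group is left out, or the frailty is placed on a unit that contains both arms, the true alpha at ICC 0.05 is about 0.15 at 18 per group and 0.12 to 0.13 at 13 to 15 per group. The nominal 95% interval is then too narrow. The inflation shrinks to about 0.07 at ICC 0.01 and vanishes at 0.0001. If a therapy-group frailty was intended in the primary model, only the wording is at fault.

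Because this is the primary analysis and the correction is small, it should be made. The abstract's design label is a separate slip and is not evidence about the primary model.

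**What to change.** In the Analysis section:

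- State that the primary hazard ratio, confidence interval and p-value come from a Cox model with a shared frailty for therapy group, or with a variance robust to clustering by therapy group and corrected for the small number of groups.
- Replace "team" with therapy group, and report the ICC from that same model.
- Use the same model for time to next manic-type episode and time to next depressive episode.

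The choice of reference distribution, and whether the frailty term stays in the model when its estimate is small, can be left to the analysis plan.

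In the abstract, reconcile the cluster-randomised label with the individual randomisation described there and in the Design and Randomisation sections.

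The cost is wording only. The interval will be wider than one that ignores groups, by a factor of up to about 1.36 at ICC 0.05 and 18 per group. The planned 179 per arm already carries the 1.85 design effect, so the sample size does not change.
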